## Abstract

The notion of a connection between autism and music is as old as the first reported cases of autism, and music has been used as a therapeutic tool for many decades. Music therapy holds promise as an intervention for individuals with autism, harnessing their strengths in music processing to enhance communication and expression. While previous randomized controlled trials have demonstrated positive outcomes in terms of global improvement and quality of life, their reliance on psychological outcomes restricts our understanding of underlying mechanisms. This paper introduces the protocol for the Music for Autism study, a randomized crossover trial designed to investigate the effects of a 12-week music therapy intervention on a range of psychometric, neuroimaging, and biological outcomes in school-aged children with autism. The protocol builds upon previous research and aims to both replicate and expand upon findings that demonstrated improvements in social communication and functional brain connectivity following a music intervention. The primary objective of this trial is to determine whether music therapy leads to improvements in social communication and functional brain connectivity as compared to play-based therapy. In addition, secondary aims include exploring various relevant psychometric, neuroimaging, and biological outcomes. To achieve these objectives, we will enroll 80 participants aged 6–12 years in this international, assessor-blinded, crossover randomized controlled trial. Each participant will be randomly assigned to receive either music therapy or play-based therapy for a period of 12 weeks, followed by a 12-week washout period, after which they will receive the alternate intervention. Assessments will be conducted four times, before and after each intervention period. The protocol of the Music for Autism trial provides a comprehensive framework for studying the effects of music therapy on a range of multidimensional outcomes in children with autism. The findings from this trial have the potential to contribute to the development of evidence-based interventions that leverage strengths in music processing to address the complex challenges faced by individuals with autism.

**Clinical Trial Registration**: Clinicaltrials.gov identifier NCT04936048.

## Introduction

1.

Autism spectrum disorder (ASD) is a highly heterogeneous, lifelong neurodevelopmental condition that is diagnosed based on behavioral criteria. It is characterized by challenges in social communication and interaction, as well as restricted and repetitive patterns of interests and behavior that significantly impact daily life (1). Autism symptoms vary extensively between individuals and can manifest differently within the lifespan of a single individual (2). The presence of co-occurring psychiatric and medical conditions further contributes to the complexity and heterogeneity of autism, making it challenging to identify effective treatment approaches for individuals (3, 4).

Currently, early and intensive behavioral interventions are recommended as the primary treatment to target core ASD symptoms (5, 6). However, these studies are limited by methodological constraints (7, 8), and the cost and demanding nature of implementing early intensive behavioral interventions pose barriers to their accessibility (9). Consequently, there are limited evidence-based treatment options available, and the sole focus on reducing core behavioral symptoms may not adequately address the multifaceted mental health needs of individuals with autism (10).

Music therapy (MT) has been used for several decades to enable communication and expression in individuals with autism (11). In contrast to difficulties in social processing, music processing has been identified as a strength and an interest for many individuals with autism since the initial descriptions of autism (12) and remains a topic of ongoing research. Studies focusing on auditory processing indicate that individuals with autism exhibit a preference for musical over verbal stimuli (13, 14). Furthermore, parental reports suggest children with autism often choose to engage in musical activities and that music elicits an enduring emotional response in them (15–17).

Beyond showing an interest in music, musical abilities have also been considered a relative strength within their global profile (18, 19). Several studies have reported better performance in individuals with autism versus controls on tasks related to pitch processing (for review, see (15)), enhanced melodic memory (17, 20, 21), and intact rhythm synchronization (22). Notably, while individuals with autism may encounter challenges in processing emotions from social stimuli (23), research suggests that they do not experience difficulties in understanding emotions expressed through music, known as musical emotions (24–26). Therefore, music processing represents a domain in which some individuals with autism exhibit strengths and a notable level of interest. Moreover, music serves as an easily accessible and widely available stimulus that effectively engages and emotionally rewards children with autism (27, 28). Thus, music therapy provides an opportunity to leverage strengths in music processing to address the challenge of developing social communication skills.

Systematic and robust scientific investigation of the effects of music therapy (MT) in this population began only recently (29). Drawing from 26 randomized controlled trials (RCTs) conducted since the 1990s, MT has demonstrated positive outcomes in terms of global improvement, symptom severity, and improved quality of life (11). However, findings from a large-scale RCT indicated that MT may not result in significant changes in core symptoms as assessed by diagnostic tools (30). It is important to note that the majority of RCTs conducted on MT thus far have primarily relied on observations of behaviors that are clinically relevant as outcome measures (9). To gain a deeper understanding of the underlying mechanisms of MT, it is crucial to establish connections between behavioral outcomes and neuroscientific measures, such as resting-state functional connectivity (RSFC) obtained from functional magnetic resonance imaging (fMRI) (31).

Resting-state functional magnetic resonance imaging (rsfMRI) is a valuable tool for studying functional connectivity (FC) in clinical and pediatric populations. Unlike task-based fMRI, which measures responses to specific tasks, rsfMRI examines the organization of intrinsic functional networks that are stable across different behavioral states (32, 33). By scanning subjects in a wakeful state without engaging in specific tasks, rsfMRI removes some cognitive demands and enables the examination of clinical populations more effectively. It also allows for scanning subjects at multiple time points, eliminating repetition effects associated with task-based paradigms (34).

RSFC studies have reported atypical connectivity within and between functional brain networks in individuals with ASD (35–37). Initial research suggested general cortical hypoconnectivity as a possible explanation for clinical symptoms in ASD (38–40). However, divergent findings have emerged, including hypoconnectivity, hyperconnectivity, and a combination of both in individuals with ASD compared to controls [for review, see (35)]. Age plays a crucial role in understanding FC in ASD, as the brain undergoes significant developmental changes that might help explain divergent findings (36). From a developmental perspective, emerging evidence suggests both short- and long- range hyperconnectivity in school-aged children with autism relative to typically developing children (36, 41–43). Although the precise characteristics of brain connectivity in ASD remain unclear, accumulating evidence suggests the involvement of both hypo- and hyperconnectivity, with children showing differences in overall FC patterns to those seen in adolescents and adults.

To date, only one randomized controlled trial (RCT), namely Sharda et al. (29), has integrated both behavioral outcomes and functional brain connectivity to evaluate the effects of music interventions on school-aged children with autism. Sharda et al. selected six target seed areas (bilateral Heschl’s gyrus, HG; inferior frontal gyrus, IFG; temporal pole, TP) based on their relevance to language and communication, as well as a prior study on perception of sung versus spoken words (44). The findings from the seed-based connectivity analysis indicated an increase in connectivity between auditory seeds (left and right HG) and striatal and motor regions, as well as a decrease in connectivity between auditory seeds (left HG and right TP) and visual areas following 8–12 weeks of music intervention compared to a non-music play-based intervention. Importantly, these changes in connectivity were correlated with improvements in social communication scores as rated by parents, providing initial evidence that music interventions can improve both social communication and functional brain connectivity in children with autism (29). However, there is a need for replication and expansion of these findings, and this is the aim of the Music for Autism (M4A) trial.

The M4A trial will investigate various additional outcomes and potential mechanisms than those studied by Sharda et al. These include exploring the impact of MT on chronic stress, an often overlooked issue among individuals with ASD (10) that has been shown to impede learning (45) and that can be modulated through musical interventions (46). The study will also examine potential structural brain changes, which are known to be influenced by psychological and biological therapies (47) as well as musical training (48). Furthermore, the research will delve into the concept of predictive processing, exploring potential links between prediction and pleasure derived from music (49), and it will examine children’s participation in the community, which is known to be limited by environmental barriers (50). Lastly, brain structure and function are closely tied to the gut microbiome (i.e., the microorganisms that inhabit the gastrointestinal tract) (51). The study aims to both examine the gut-brain axis in children with ASD (52, 53) and to explore whether music therapy intervention could serve as a potential modulator of effects.

### Aims

1.1.

The primary aim of the Music for Autism (M4A) trial is to investigate whether a 12-week music therapy intervention, compared to play-based therapy, can lead to improvements in social communication and functional brain connectivity in school-aged children with autism. Secondary aims include examining the effects of MT on a range of psychometric, neuroimaging, and biological outcomes in children with autism.

We hypothesize that a 12-week music therapy (MT) intervention, compared to play-based therapy (PT), will lead to the following outcomes in children with autism aged 6–12:

1. Psychometric outcomes:

Significant improvements in *social communication* (primary).Increased *participation* in home, school, and community life.Improvements in *family quality of life*.Increased *adaptive behaviors*.Improvements in *receptive vocabulary* skills.Improvements in *social functioning*.Improved *prediction* accuracy.

2. Neuroimaging outcomes:

Changes in *resting-state functional connectivity* (primary), characterized by:Increased coupling between auditory and both striatal and motor regions.Decreased coupling between auditory and visual regions.Increased whole-brain *grey and white matter volume.*

3. Biological outcomes:

Reduced hair cortisol concentration, indicating a decrease in *chronic stress*.Alterations in *gut microbiome* composition and an association between changes in gut microbiome composition and changes in neuroimaging and psychometric outcomes.

Furthermore, we anticipate that the observed changes in functional connectivity will correlate with the primary outcome of improved social communication skills.

## Methods and analysis

2.

### Study design

2.1.

M4A is an international, assessor-blinded crossover RCT comparing music therapy (MT) to a structurally matched play-based therapy (PT) intervention, combining psychometric, neuroimaging and biological outcome measures (Figure 1).

**Figure 2 fig2:**
[figure not shown]
Flow of participants through the study: illustration of the study design. T1, Baseline assessment/pre-intervention at 0 months; T2, Post-intervention 1 at 3 months; T3, Pre-intervention 2 at 6 months; T4, Post-intervention 2 at 9 months.

### Participants

2.2.

Inclusion criteria are being 6–12 years old and having an ASD diagnosis from a licensed health professional with an ICD code (54), ideally supported with scores of standardized tools [ADOS (55), ADI-R (56)] and assessment of intelligence quotient (IQ) or level of ability. Exclusion criteria include individual MT during the last 6 months; generalized epileptic seizures during the last 12 months; more than 12 months of cumulative music training; or conditions precluding fMRI scanning (such as metallic or electronic implants, claustrophobia, hyperacusis, or persistent problems in complying with scanning procedures).

#### Recruitment

2.2.1.

Participants will be recruited in two cities (Bergen, Norway; Vienna, Austria) by advertising through social media and reaching out to relevant groups such as parent associations, schools, clinicians, and special educators.

#### Enrollment and randomization

2.2.2.

When possible, enrollment will be scheduled so that interventions will take place during the school year and washout periods during school holidays. We expect to randomize around 27 participants each half year in both sites combined. Computer-generated randomization lists, with randomly varying block sizes of 4–6, separate for each country, will be used to ensure both unpredictability and balance. The lists will be generated by a researcher who does not have contact with participants and are stored centrally, concealed from clinical investigators, until a decision on inclusion is made. Once a participant is enrolled, the randomization result will be conveyed to clinical investigators through an online system (Research Electronic Data Capture (REDCap) on Norwegian Research Centre (NORCE) servers).

### Interventions

2.3.

Locations (a dedicated room at each site) and materials (matched to those in Sharda et al. as closely as possible) will be standardized to ensure consistent implementation in Bergen and Vienna. Both interventions will consist of 12 weekly one-on-one sessions, 45 min each, conducted in the same setting by a licensed music therapist. In sum, both MT and PT use a developmentally oriented approach with the overall aim of improving quality of life (57) and targeting creating a shared experience, building meaningful relationships, and fostering self-expression. A varied set of activities, combining therapist- and child-led interactions, target common goals including sensory processing, emotional development, and social communication.

Children can choose 4 activities per session using pictures of the activities and a visual schedule to facilitate communication and provide structure to the sessions (58). MT uses rhythmic cues, musical instruments (e.g., piano, djembe, xylophone, ukulele), songs, and stories accompanied by songs. PT is designed as a play-based active comparison condition to control for factors such as support, therapist attention, positive expectancies, and emotional engagement. It uses verbal interaction, toys (e.g., building bricks, finger puppets, plasteline, puzzles), and stories without a musical component.

Treatment fidelity (59, 60) will be monitored and ensured via therapists’ reports, supervision meetings, and video recordings of sessions. For every child, three videos from each intervention arm (first, middle, and last session) will be assessed by two independent raters. The fidelity checklist covers dimensions such as dose (e.g., number of sessions); structure (e.g., number and type of activities); content (e.g., use of musical or verbal reinforcements); and processes (e.g., therapist’s attunement, therapist’s responsiveness). In addition, child engagement and interaction levels will be investigated. Differentiation between MT and PT will be analyzed by comparing the amount of musical and verbal reinforcement used.

#### Psychometric outcomes

2.4.1.

Psychometric outcomes include: (1) social communication (primary); (2) participation; (3) family quality of life; (4) receptive vocabulary; (5) social functioning; (6) adaptive behavior; and (7) predictive processing. Participation and family quality of life are the two main secondary psychometric outcomes because of their particular importance to participants. All outcomes except social communication, receptive vocabulary, and predictive processing are parent-rated.

(1) *Social communication* as assessed by a blinded assessor using the Children’s Communication Checklist 2nd Edition (CCC-2) (61, 62) will be the primary psychometric outcome. The CCC-2 measures aspects of pragmatic communication with 70 items across 10 subdomains (speech, syntax, semantic, coherence, inappropriate initiation, stereotyped language, use of context, nonverbal communication, social relations, and interests) and has shown high interrater reliability and internal consistency (40). The General Communication Composite (GCC) standard score is standardized to *M* = 100 (SD = 15), with higher scores indicating better social-communication skills (reversed from raw scores). Whereas Sharda et al. relied on parent reports for this outcome, where attempted blinding was unsuccessful (29), M4A relies on a special educator/teacher who knows the child well. Success of blinding will be verified at the last follow-up by asking the assessor about incidental unblinding.(2) *Participation* is measured using the Child and Adolescent Scale of Participation (CASP), a caregiver-report scale consisting of 20 items across four subdomains (home participation, community participation, school participation, home and community living activities) (63). The scale has high test–retest reliability and internal consistency. The 20 items are rated on a four-point scale from 1 (unable to participate) to 4 (age-expected/full participation). Parents can indicate if any of the items does not apply to them. The sum of all applicable items is then divided by the maximum possible sum score (as given by the number of applicable items) and multiplied by 100 to produce a score with a possible range from 0 and 100. Higher scores indicate more participation.(3) *Family quality of life* is measured using the Beach Center Family Quality of Life Scale (FQoL) (64), a 25-item scale to measure families’ perceived satisfaction in terms of quality of family life (including family interaction, parenting, emotional well-being, physical/material well-being, and disability-related support). Parents rate each item on a 5-point scale from 1 (very dissatisfied) to 5 (very satisfied) for a total sum score from 25 and 125, with higher scores indicating better quality of life.(4) *Receptive vocabulary* is measured with the Peabody Picture Vocabulary Test-4th edition (PPVT-4) (65, 66), conducted by a qualified health professional. The assessment with up to 228 items (each with a spoken word +4 pictures to choose from) produces raw scores which are then converted to standard scores using a conversion table. We will use German norms in Austria, and American norms (in the absence of Norwegian norms) in Norway. The German manual deviates from the American manual in suggesting T-scores (50 ± 10) instead of standard scores (100 ± 15); however, we will convert all T-scores to standard scores [i.e., (x–50)*1.5 + 100 for the Austrian data] to ensure comparability. Handling of extreme values is also different: While the American norms used in Sharda et al. and in the Norwegian M4A sample allow for a wide range of scores, Austrian standard scores are cut off at ±2.3 SD according to the German manual (65). Higher scores indicate better receptive vocabulary.(5) *Social functioning* will be assessed through the Social Responsiveness Scale (SRS-2) (67). Parents are asked to rate 65 items associated with behaviors observed in autism (in 5 subdomains: social awareness, social communication, social motivation, social cognition, and restricted and repetitive behaviors), each from 1 (not true) to 4 (almost always true). Total raw scores are converted into T-scores (50 ± 10) through a conversion table. Higher scores on the SRS indicate greater social difficulties, while lower scores indicate better social functioning. The instructions normally ask respondents to consider the past 6 months; we adjusted this to the past 6 weeks to match our intervention periods.(6) *Adaptive behavior* will be assessed using the Vineland Adaptive Behavior Scales, 3rd Edition (Vineland-3) (68). It is a comprehensive parent-rated assessment tool used to measure adaptive behavior and to support the diagnosis of intellectual and developmental disabilities, autism, and developmental delays. Vineland maladaptive behavior as well as gross and fine motor skills are reported as v-scale scores (standardized 15 ± 3 in the general population). In addition to the domains used by Sharda et al., M4A also uses the Adaptive Behavior Composite (ABC) standard score (100 ± 15), from the domains of communication, daily living skills, and socialization, as a measure of overall adaptive functioning level. Higher adaptive behaviors and gross and fine motor skills scores, and lower maladaptive behavior scores, represent better outcomes.(7) *Predictive processing* will be assessed through two behavioral prediction tasks. Children will be asked to complete two tasks on a computer: a music prediction task, and an action prediction task to evaluate (a) their ability to learn stimulus-outcome associations with both music stimuli and the actions of others; and (b) the degree of pleasure they derive from successful predictions. Both tasks combined last around 40 min.

In the music prediction task, children will be presented with different music pieces that will end either in an expected, consonant way, or with an unexpected, dissonant sequence of tones. Each type of music is associated with the portrait of one composer (in a comic drawing style) in the training phase. In the experimental phase, children are asked, after listening to the music, how much they like the music and which of the two composers was playing it.

In the action prediction task, children are presented with several videos displaying the unfolding of an action: taking or giving an apple or a glass of water. Each action is predicted by environmental cues (e.g., red or violet plate for the apple, white or blue tablecloth for the glass). During the task children are asked to guess from an initial static picture whether the action is taking or giving (by taking into consideration the changing cue), how sure they are of their choice and, after seeing the video, how much they liked it.

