### Risk mitigation

3.1.

Slow recruitment is the biggest risk for the trial. The teams in Bergen and Vienna can draw on a history of successful recruitment for ASD studies (30) that support the feasibility of recruitment for M4A. We anticipate slower recruitment in Bergen relative to Vienna given that Bergen is a smaller city with a smaller population. Thus, recruitment can be extended from Bergen to other cities if needed throughout the trial. Furthermore, participation in the trial requires the ability to lay still in the scanner, which can be difficult for many children who would otherwise be eligible. To increase the likelihood of participation, we will offer tools and preparation for eligible children and families prior to the baseline scan.

An additional set of challenges is associated with the trial being a multinational replication study. These include language barriers, the availability of assessments in each language, but also variations in scoring procedures and scales requiring adaptations for consistency. The CCC-2 in Vienna; PPVT-4 in Norway; CASP in Vienna; and FQoL in both countries, will be translated in-house. The measures will be translated and back translated by independent researchers to ensure the accuracy of the content.

Adequate timing of interventions and follow-ups in trials such as the M4A provides logistical challenges as it requires the collaborative and timely effort of many people involved – therapists, parents, teachers, children, assessors, radiologists, and researchers. To ensure timely completion of assessments, planning and follow-up procedures will be implemented across sites.

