### Potential impact

3.3.

By conducting a replication study in a different cultural context, employing a larger sample size, and incorporating additional measures, the M4A trial may reinforce the initial findings of improved social communication and resting state functional connectivity among a cohort of school-aged children with autism following a music therapy (MT) intervention (29). Additionally, the study has the potential to advance our understanding of the biological mechanisms underlying MT and its associations with psychometric outcomes.

MT is considered a low-risk intervention for children with autism, as it has minimal side effects (11, 30) and is often more accessible compared to invasive approaches like medication or costly interventions such as early intensive behavioral intervention. Despite the positive outcomes indicated by recent systematic reviews on MT for individuals with autism, there remains a need for further studies to explore the impact of MT on functional brain connectivity. Currently, the existing empirical studies focusing on MT’s effects on brain connectivity in children with autism are limited to the trial conducted by Sharda et al., which the M4A study aims to replicate. By specifically isolating the effects of MT, M4A’s findings hold the potential to enhance our understanding of how MT influences functional brain connectivity as well as other biological outcomes among school-aged children with autism.

Considering the inclusive nature of M4A, which aims to recruit children with varying levels of functioning, the study results have the potential to offer valuable insights into the effects of MT on different subgroups within the autism population. This, in turn, could contribute to a more refined selection of suitable cases. Understanding the complex relationships between clinically or neuroscientifically defined subgroups and treatment outcomes requires additional analyses. Advanced techniques such as machine learning can be applied to extract meaningful patterns from the comprehensive dataset. Moreover, data-driven methods, including resting-state fMRI analysis techniques like graph theory and dynamic functional connectivity, can offer alternative ways to process and interpret the data.

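### PPVT-4 standard scores are cut off at ±2.3 SD in Austria but keep a wider range in Norway, and the protocol discloses this without a remedy, which biases the exploratory vocabulary effect toward zero by an unknown amount

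*Protocol article*

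**What the plan says.** Section 2.4.1 (Psychometric outcomes) of the protocol article describes the PPVT-4 as an assessment of up to 228 items that "produces raw scores which are then converted to standard scores using a conversion table". The norms differ by country: "We will use German norms in Austria, and American norms (in the absence of Norwegian norms) in Norway". Because the German manual reports T-scores, the protocol adds: "we will convert all T-scores to standard scores [i.e., (x–50)*1.5 + 100 for the Austrian data] to ensure comparability". The next sentence says that extreme values are also handled differently. The American norms permit a wide range, whereas "Austrian standard scores are cut off at ±2.3 SD according to the German manual". Nothing is said about what the analysis will do with scores at the limit.

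Section 2.7.2 (Data analysis plan) applies one model to every continuous outcome: an ANCOVA of the within-child post-test difference (music therapy minus play therapy) on the within-child pre-test difference. As written it has no site term, no period term and no provision for censored scores. Section 2.7.3 places receptive vocabulary among the remaining secondary outcomes, which are exploratory.

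Two statements bear on how many children may be affected. Section 3.3 says the trial "aims to recruit children with varying levels of functioning". Section 3.1 says "We anticipate slower recruitment in Bergen relative to Vienna", so the site with the cut-off is expected to supply the larger share.

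**The concern.** A linear conversion from T-scores to the 100 ± 15 metric puts both countries on the same unit. It does not give them the same range. Comparing each child with himself or herself cancels a constant difference between norms or sites, but it does not cancel clipping.

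An Austrian child whose true score lies below the limit at all four visits has the same recorded score each time and contributes a difference of exactly zero. A child below the limit after one intervention and above it after the other shows only the part of the change above the limit. A Norwegian child at the same level can show more of it.

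Improved receptive vocabulary is one of the stated hypotheses (section 1.1). A null result, or an apparent difference between Vienna and Bergen, could then partly reflect the scoring manual. The loss falls mainly on children with low language.

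**Working it through.** **Inputs from the protocol.** Cut-off ±2.3 SD; conversion (T − 50) × 1.5 + 100; the within-child ANCOVA of section 2.7.2.

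**Assumptions, because the protocol gives no figures.** True PPVT-4 scores normal with mean 70 to 100 and SD 15 to 25; Vienna share 50% to 70%; correlation between visits 0.8 to 0.9; true effect 0.34 SD. The value 0.34 is borrowed from the power calculation in section 2.7.1, which concerns the CCC-2.

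**Step 1: the limits.** ±2.3 SD on the T scale is 50 ± 23, that is 27 and 73. The protocol's formula gives (27 − 50) × 1.5 + 100 = 65.5 and (73 − 50) × 1.5 + 100 = 134.5.

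**Step 2: share of a mean shift that survives clipping.** When a normal score is clipped to the range from L to U, its clipped mean rises, per unit shift in the true mean, by P(L < X < U). For a shift δ, the retained fraction is the average of this probability as the mean moves from m to m + δ. With random allocation to sequence and no carry-over, the expected pre-test difference is zero. The ANCOVA intercept then has the same expectation as the mean post-test difference, and the correlation between visits does not affect it.

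Example, mean 80 and SD 15: δ = 0.34 × 15 = 5.1.
- At 80: Φ(54.5/15) − Φ(−14.5/15) = 0.833.
- At 85.1: Φ(49.4/15) − Φ(−19.6/15) = 0.904.
- Average: about 0.87.

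**Step 3: pooling.** With Vienna share w and retained fraction R, the pooled fraction is 1 − w(1 − R). For R = 0.87 this is 1 − 0.5 × 0.13 = 0.935 at w = 0.5, and 1 − 0.7 × 0.13 = 0.909 at w = 0.7.

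| Assumed mean, SD | At or below 65.5 | Retained, Austria | Pooled, 50% Vienna | Pooled, 70% Vienna |
|---|---|---|---|---|
| 100, 15 | 1% | 98% | 99% | 98% |
| 90, 15 | 5% | 96% | 98% | 97% |
| 85, 20 | 16% | 86% | 93% | 90% |
| 80, 15 | 17% | 87% | 94% | 91% |
| 75, 20 | 32% | 74% | 87% | 82% |
| 70, 25 | 43% | 63% | 81% | 74% |

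A simulation of the section 2.7.2 model with Austrian scores clipped gives the same fractions. The loss has the same direction in every scenario.

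**Step 4: standardised scale.** Clipping also shrinks the residual variance, so the effect divided by the residual SD falls less. With 60% in Vienna and a visit correlation of 0.8:
- Mean 80, SD 15: from 0.535 to 0.517, a fall of 3%. The pooled mean falls by 0.6 × 13% = 8%.
- Mean 70, SD 25: from 0.539 to 0.476, a fall of 12%. The pooled mean falls by 0.6 × 37% = 22%.

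**Step 5: who shows no change.** Below the limit at all four visits are about 0.1% of children in the mildest scenario and 26% in the most severe. Of those at the floor after play therapy, about 35% to 78% are above it after music therapy with the assumed gain.

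**The case against.** **Disclosure.** A reader might infer that the protocol contradicts its own claim of comparability. It does not. The comparability wording is attached to the T-score conversion, and the following sentence volunteers that extremes are handled differently. Section 3.1 also acknowledges scoring variations between the countries. This is an open limitation left unresolved. Nor does the text say that American scores are unlimited, only that their range is wide.

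**No change at all.** It is also tempting to say that low-scoring Austrian children cannot show change. That holds only for children beyond the limit at every visit compared; many others cross it and show part of the change (Step 5). For the same reason the Austrian loss is smaller than the share at the floor: 13% against 17%, and 37% against 43%.

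**Size.** The protocol gives no PPVT-4 distribution and no site split. Section 2.2 excludes children with persistent problems in complying with scanning, and section 3.1 notes that lying still is hard for many otherwise eligible children. This may thin out the lowest scorers, so the severe scenarios may not arise. This objection stands: a material dilution is possible but not shown.

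**Consequence.** Vocabulary is neither primary nor one of the two main secondary psychometric outcomes, and no site comparison is planned in section 2.7.2. This also stands and limits the priority.

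**Raw scores have costs.** Matching visits in the two periods are six months apart. Age norms remove expected growth, the planned model has no period term, and standard scores serve replication of the earlier trial. This is a good reason not to replace the standard score, but not a reason to omit a second analysis.

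**Left to the analysis plan.** Handling of limit scores could appear in a document not shown. The article nevertheless fixes the analysed score, the conversion and the cut-off, and followed as written these produce the bias.

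**Conclusion.** The point holds in a limited form. The analysed vocabulary score has a narrower range in Austria than in Norway, the conversion cannot repair that, and the within-child model does not cancel it. The mean effect is biased toward zero in Vienna and hence in the pooled analysis.

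The direction follows from the protocol's own scoring rules, given an effect that shifts scores. The size does not: about 1% to 26% of the pooled mean difference, resting on the assumed means, SDs, 0.34 SD effect and Vienna share listed above, and less on the standardised scale. The document does not support saying that the vocabulary result is seriously diluted. It supports saying that a null result or a site difference could not be interpreted safely without a further analysis. The primary outcomes, the sample size and the confirmatory tests are untouched.

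**What to change.** 1. Keep the PPVT-4 standard score as the reported outcome, for comparability with the earlier trial.
2. Pre-specify beside it a within-child analysis of the PPVT-4 raw score, which already exists as the input to the norm tables. Divide it by the country-specific baseline SD, because the two language versions differ. Add a sequence indicator coded ±½ to the section 2.7.2 model as the period term, so that the intercept remains the treatment effect while growth with age is absorbed. A censored-data model for the standard score, with the Austrian limits at 65.5 and 134.5, is an acceptable alternative.
3. Report the number of children at each limit by country and visit.
4. State that neither a null vocabulary result nor a difference between the sites will be interpreted without the analysis in item 2.

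The cost is one additional analysis and a short paragraph in the analysis plan, with no new data. Raw-score growth over the six months between matching visits differs between children and adds some variance, and the raw-score result is less directly comparable with the earlier trial. That is why it stands beside the standard score and does not replace it.
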